**TNSS**			
**Pre-intervention**	9.7±2.2	9.5±2.0	10.1±1.7
**Post-intervention**	5.1±1.7^*^	7.1±1.9^*#^	7.3±1.6^*#^
**Running nose**			
**Pre-intervention**	2.5±0.5	2.4±0.7	2.6±0.5
**Post-intervention**	1.4±0.5^*^	1.7±0.5^*^	1.9±0.6^*^
**Itching**			
**Pre-intervention**	2.6±0.7	2.5±0.8	2.6±0.7
**Post-intervention**	1.5±0.8^*^	1.9±1.1^*^	1.8±0.4^*^
**Nasal obstruction**			
**Pre-intervention**	2.2±0.9	2.3±1.1	2.5±1.1
**Post-intervention**	0.8±1.0^*^	1.7±1.1^*#^	1.7±0.9^*#^
**Sneezing**			
**Pre-intervention**	2.4±0.8	2.3±1.1	2.4±0.7
**Post-intervention**	1.4±0.7^*^	1.8±0.9^*^	1.8±0.4^*^

^*^Compared with Pre-intervention *P*<0.05. ^#^Compared to the ARAT group *P*<0.05

*ARAT* Allergic Rhinitis Acupressure Therapeutic, *TNSS* Total nasal symptom score

### Randomization and blinding

#### Randomization

The randomization sequence will be generated by the Key Unit of Methodology in Clinical Research at SCCGZUCM. The random numbers will be generated using the SAS statistical analysis system PROCPLAN process statement, with the numbers generated based on given seeds. The randomization process will be managed through computer network management, and a dedicated manager who is not involved in the study will control the distribution scheme. The eligible participants will be assigned random numbers in the order of their entry into the study, and the researchers will allocate them to the treatment group or control groups accordingly.

After collecting written informed consent, the 111 participants will be randomly divided into three groups, with 37 participants in each group.

### Blinding

Considering the significant contrast in content between the treatment and control groups and the lack of an impact on the therapy's final effects, blinding procedures will not be applied in this trial. Therefore, both the investigators and the participants will be aware of the type of intervention during the clinical trials.

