#### Secondary outcome measures

The secondary outcome measures in this clinical trial will include the following assessments: Rhinoconjunctivitis Quality of Life Questionnaire score (RQLQs), acoustic rhinometry (AcRh), anterior rhinomanometry (AnRh), relief medication scores (RMs) and adverse events (AEs).

RQLQs is a questionnaire a questionnaire used to assess patients' quality of life, and consists of 28 questions grouped into seven domains, including activities, sleep, non-nose/eye symptoms, practical problems, nasal symptoms, eye symptoms, and emotional well-being. Each domain is ranked from no impairment to severe impairment on a scale of 0 to 6 [3, 8, 31]. The severity of symptoms during the trial will also be assessed using TNSS.

AcRh is a noninvasive and reliable method for studying the nasal cavity. It measures cross-sectional area and volume by analyzing acoustic reflections at various distances from the nasal inlet [32]. AcRh has been used to evaluate nasal dimensions in AR and assess the effectiveness of therapeutic interventions [33].

AnRh is a method designed to analyze the airflow through one nostril at a time based on trans nasal pressure. It is used to assess nasal air-space volume and patency and has become an international standard for estimating nasal resistance and flow [34].

RMs will be considered in evaluating the efficacy of the trial. The daily dose of anti-allergic medication, including antihistamines, decongestant nasal sprays, and eye drops, will be scored as 1 point. Orally administered antihistamines will be scored as 2 points, and steroid nasal sprays or eye drops will be scored as 3 points [35].

AEs will be monitored through self-reporting by the participants. Any undesirable experiences will be recorded on Case Report Forms (CRFs). Participants will have access to the research team for any concerns or issues. The occurrence time, severity, management, and causal relationship of AEs will be documented. All AEs will be followed up until resolution, and severe AEs will be promptly reported to the Ethics Committee of SCCGZUCM within 24 hours. A questionnaire will also be used to gather participants' opinions on the expectations of self-administered acupressure for AR and the credibility of the blinding method used in the study.

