Additionally, the treatment mechanism of ARAT will be explored in this trial. Nasal secretions from eligible participants will be collected by research nurses at the beginning and end of the treatment. These biological specimens will be centrifuged and stored in the Biological Resource Center of SCCGZUCM for molecular analysis. Cytokines such as interleukin-5 (IL5), IL13, thymic stromal lymphopoietin (TSLP), and interferon-gamma (IFN-γ) will be detected using the enzyme-linked immunosorbent assay (ELISA) method.

Among these outcome measures, TNSS and RQLQs will be assessed at the beginning, middle, and end of treatment period, as well as during the follow-up period at weeks 4, 8, and 12. The other measures will be assessed at the beginning and end of the treatment period.

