### Statistical analysis

Qualified statisticians who are blinded to the treatment group data will perform all efficacy and safety analyses following the intention-to-treat (ITT) principle using SPSS 20.0 (IBM SPSS Inc., Armonk, New York, USA). Missing values will be estimated using the last recorded data. A significance level of α= 0.05 will be considered statistically significant. The median, minimum, and maximum values will be used to express measured data. Group comparisons will be analyzed using Analysis of Variance (ANOVA) and pairwise comparisons (rank-sum test for univariate variance). Count data will be expressed as composition ratios or rates, and comparisons between groups will use the χ2 test for efficiency and rank-sum test for efficiency and rank-sum test for ranked data.

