To the best of our knowledge, this is the first clinical trial of comparing self-administered specific acupoint acupressure group and a blank control group. Additionally, it is the first trial to monitor the process online. Blinding of researchers and participants is not possible due to the nature of acupressure; however, participants will be blinded during the entire randomization process. Although non-specific acupoints have not been reported for the treatment of AR, investigation is needed to determine the therapeutic effects of acupressure on these non-specific acupoints in this trial. This trial also represents the first attempt to explore the mechanism of acupressure for PAR by analyzing and comparing cytokines in nasal secretions. It is expected to contribute valuable knowledge to fill the gaps in research. Compared to previous studies on acupressure for PAR, this trial features several innovations and advancements, including clearer diagnostic criteria for PAR classification and a more rigorous methodology. To ensure a well-designed trial, the following aspects were considered: random allocation to prevent selection bias and assessment of trial outcomes using both clinician-administered and self-reported measures.

There are certain limitations in this trial. First of all, a sham acupoint control group will not be established due to difficulties in defining sham acupoints. Secondly, individual differences in the sensitivity of acupoints and the applied pressure strength are not uniform, warranting a larger sample size to identify patterns in acupressure for AR. In this protocol, we have described a three-arm, randomized, controlled trial to examine the safety and efficacy of ARAT in treating PAR. This study will provide reliable information on the therapeutic effects of ARAT and help elucidate its potential immunologic mechanism.

In conclusion, this trial offers a standardized and practical protocol to guide current and future research. Furthermore, it contributes to the accumulation of clinical experience regarding acupressure on specific acupoints. By investigating the effectiveness and safety of acupressure, the findings of this trial are expected to provide positive evidence in support of its use for PAR patients. Moreover, the results will offer valuable insights for healthcare professionals in managing PAR symptoms.

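### Blinding is waived for everyone but the statisticians, on grounds that do not reach the staff who measure rhinometry, rhinomanometry and cytokines, so these outcomes carry avoidable measurement bias

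*Protocol article*

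**What the plan says.** The Blinding section gives a general rule: "blinding procedures will not be applied in this trial. Therefore, both the investigators and the participants will be aware of the type of intervention". It offers two grounds. One is the marked contrast in content between the arms. The other is "the lack of an impact on the therapy's final effects", for which no support is given.

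Three other places speak of blinding:

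- **Statistical analysis:** "Qualified statisticians who are blinded to the treatment group data will perform all efficacy and safety analyses".
- **Discussion:** "Blinding of researchers and participants is not possible due to the nature of acupressure; however, participants will be blinded during the entire randomization process".
- **Secondary outcome measures:** a questionnaire will ask participants how credible they found the study's blinding method.

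On the outcomes concerned, Secondary outcome measures says of acoustic rhinometry that "AcRh has been used to evaluate nasal dimensions in AR and assess the effectiveness of therapeutic interventions", and describes anterior rhinomanometry as an international standard for nasal resistance and flow. On the cytokines it says: "Nasal secretions from eligible participants will be collected by research nurses at the beginning and end of the treatment". The specimens are then centrifuged and stored at the institution's biological resource centre before the ELISA. Nowhere does the article provide for a masked device operator or for coded samples.

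**The concern.** Participants in this trial know their arm, and most of the outcomes are what they report. If ARAT looks better on symptoms or quality of life, expectation is a competing explanation that the analysis cannot remove. Rhinometry, rhinomanometry and the cytokines are the outcomes that do not pass through the participant's own rating, so they offer the best check on that explanation. The title's reference to nasal mucosal function and the stated aim of exploring a mechanism both rest on them.

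That check is worth most when whoever takes the reading does not know the arm. The plan gives up this protection by a general rule, although its reasons concern the people who perform or teach acupressure and not those who take the readings.

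**Working it through.** **Step 1. Who produces each outcome, and does that person know the arm under the Blinding section?**

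| Outcome | Source according to the protocol article | Arm known? |
|---|---|---|
| TNSS (primary) | self-assessed by the participant | yes, unavoidably as designed |
| Rhinoconjunctivitis quality of life | patient questionnaire | yes, as above |
| Relief medication score | participant diary (Ethical approval section) | yes, as above |
| Adverse events | self-report | yes, as above |
| Acoustic rhinometry, anterior rhinomanometry | instrument reading | not masked under the general waiver |
| IL-5, IL-13, TSLP, IFN-γ | secretions collected by research nurses, then ELISA | not masked under the general waiver |

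Only the last two rows do not depend on a participant's report.

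**Step 2. Do the stated grounds reach those two rows?** The contrast between arms is visible to the participant and to whoever teaches the technique. The Discussion's ground is the nature of acupressure. Under the Intervention section, participants treat themselves at night, after instruction from therapists and with weekly video calls. Taking a rhinometry reading or running a plate involves none of this. The remaining ground, that blinding would not affect the outcome, is an assertion.

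**Step 3. Is masking feasible here?** For the ELISA, yes: specimens are spun and stored before analysis, so a coded label can be applied between collection and assay. For rhinometry and rhinomanometry it is harder, because the participant is present and may disclose the arm. It requires an operator who does not train that participant and a request not to mention the arm. Nurses need attention in the roster: they collect the secretions, deliver the health education and appear in the acupressure video. The trial already accepts masking for its statisticians, but that protects the analysis and cannot undo a shift that entered at measurement.

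**Step 4. Do the blinding statements agree?** No. One section says no blinding procedures will be used. Another blinds the statisticians. The Discussion says participants are blinded during randomization. A questionnaire is to rate a blinding method that the Blinding section says will not be applied.

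**Step 5. Size.** The article gives no figure from which the size of any measurement bias could be derived. The following shows sensitivity only and rests on an assumed shift of δ SD in favour of ARAT, with no true difference. For a two-sample t-test with n = 37 per arm (Sample size section) and two-sided α = 0.05:

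- degrees of freedom = 2 × 37 − 2 = 72; critical value 1.993
- non-centrality = δ × √(n/2) = δ × √18.5 = δ × 4.301

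| Assumed δ (SD) | Non-centrality | Probability of a false-positive result |
|---|---|---|
| 0 | 0 | 5% |
| 0.1 | 0.43 | 7.1% |
| 0.2 | 0.86 | 13.6% |
| 0.3 | 1.29 | 24.7% |

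The same figures would follow for any outcome in any trial with 37 per arm. They show what a shift would do if there were one, and are no estimate of the shift in this trial.

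**The case against.** The best case for the plan has four parts.

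- **Masking is not wholly absent.** A reader might infer that the trial drops all masking. The article does not support that, since the statisticians are blinded. This stands, and the point is confined to measurement.
- **The sentence names investigators and participants, not device operators or laboratory staff.** Sample labelling and laboratory procedure are commonly left to a fuller document that is not shown, so a reader cannot conclude that the ELISA reader will in fact see the arm. This has force, more for the ELISA than for rhinometry. The point survives because the article states a waiver without exception. It is not merely silent, and the waiver as worded permits unmasked measurement.
- **The outcomes are secondary or exploratory, and read by instrument or assay.** The article calls acoustic rhinometry reliable and describes no route by which an operator could influence a reading. Influence through technique, repeated readings or handling of out-of-range values is plausible on general grounds but is not documented here. Exposure is likely to be smaller than for an observer-rated scale, and the trial's main conclusion rests on TNSS, which masked operators would not protect. This stands and lowers the weight of the point.
- **Masking is not free.** A reader might infer that it costs nothing. The article gives no staffing figures, and masking the operator needs a roster rule and participants' cooperation. This stands: the cost is small but not zero.

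**Conclusion.** The point holds in a limited form. The Blinding section waives masking for all but the statisticians, and its grounds do not extend to those who measure rhinometry, rhinomanometry and cytokines. These are the only outcomes not reported by participants who know their arm, so the waiver leaves them open to a measurement bias that could cheaply be reduced.

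The size of that bias is unknown. It would be wrong to read the 7.1% to 24.7% range as this trial's false-positive rate, because the assumed shifts have no anchor in the article. Nor does the article show that the readings will be biased, only that the rule allows it. The conclusion assumes that the Blinding section means what it says and that no fuller document overrides it for measurement staff. The change is worth making because it is inexpensive and supports the mucosal function and mechanism claims. It does nothing for the self-rated primary outcome.

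**What to change.** 1. **Blinding section.** Limit the waiver to participants and the staff who train or call them. Remove or justify the statement that blinding has no bearing on the effect.
2. **Cytokines.** Label secretion tubes with a code, and release the arm list to the laboratory only after the ELISA results are locked.
3. **Acoustic rhinometry and rhinomanometry.** Within existing staff, have the measurement made by someone who sees only the study ID and visit and does not train that participant. Ask participants not to mention their arm.
4. **Consistency.** Reconcile the Blinding section with the credibility questionnaire in Secondary outcome measures, the blinded statisticians in Statistical analysis, and the Discussion's statements on blinding.

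The cost is a few sentences of text, coded labels and a roster rule, with no new visits or procedures. If existing staff cannot cover step 3, step 2 can be done alone. The Trial status section has recruitment starting on July 1, 2023, so rhinometry readings already taken cannot be masked in retrospect. Stored secretions not yet assayed can still be coded.

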### Intervention

#### Health education

All eligible participants in the three groups will receive a comprehensive health education program on the introduction and management of PAR, conducted by research nurses. The program will be delivered through a video that will be accessible to participants via an app for convenient review.

#### Drugs

Participants in all three groups will be administered the same medication, which is mometasone furoate nasal spray (50μg once daily, Zhejiang Xianju Pharmaceutical Co., Ltd., Batch number: H20113481), as the routine treatment during the intervention period. Additionally, for symptom control throughout the study, participants will use cetirizine hydrochloride tablets (10mg, Chengdu LEER Pharmaceutical Co., Ltd., Batch number: H20020250).

#### Acupoints

Both in the treatment group and the non-specific acupoint group will apply self-administered acupressure to 10 specific acupoints, consisting of 7 acupoints on the head and neck and 3 acupoint on the limbs.

In the treatment group, the acupoints of ARAT, which have been used frequently used to alleviate nasal and non-nasal symptoms of PAR, will be slected for participants. These acupoints include *Yingxiang* (LI20), *Bitong* (EX-HN8), *Jingming* (BL1), *Yintang* (EX-HN3), *Baihui* (DU20), *Fengchi* (GB20), and *Dazhui* (DU14) as well as three acupoints on the limbs: *Hegu* (LI4), *Lieque* (LU7) and *Zusanli* (ST36) (Fig. 2). The selection of these acupoints is based on a review of classical and modern literature [15, 23–26].

**Fig. 2 Fig2:**
[figure not shown]
The Location of 10 acupoints of Allergic Rhinitis Acupressure Therapeutic

In the non-specific acupoint group, true acupoints that are not specifically indicated for treating AR according to the literature will be used. These acupoints include *Dicang* (ST4), *Jiache* (ST6), *Ermen* (SJ21), *Xiaguan* (ST7), *Chengjiang* (CV24), *Yifeng* (SJ17), *Naohu* (DU17), *Laogong* (PC8), *Neiguan* (PC6), and *Dubi* (ST35) (Fig. 3).

**Fig. 3 Fig3:**
[figure not shown]
The Location of 10 Non-specific Acupoints

The acupoints, along with their Chinese pinyin names as per the World Health Organization (WHO) acupuncture nomenclature, can be easily located based on the provided guideline [27].

#### The treatment group (The ARAT group)

At the start of the intervention, the therapists will provide individualized, face-to-face instructions and training on ARAT techniques to each participant in the treatment group.

A video will be created that that includes lectures, demonstrations, and practice sessions conducted by nurses and therapists, demonstrating the correct acupressure techniques. This video will be uploaded to the app for participants to access.

Participants in the treatment group will perform self-administered acupressure on the designated acupoints for approximately 10 minutes every night, either after bathing or before sleeping. Participants will undergo 20 sessions treatment for 4 weeks. They will apply pressure to each acupoint 60 times, completing the entire session within the allocated time. Participants should apply sufficient pressure to experience a sensation of pressure, warmth, and slight soreness. The app will contain the video, which will be distributed to each participant. Participants will be asked to check-in at the start and end of each session.

Throughout the treatment period, participants will undergo weekly video-call check-ins to monitor their acupressure technique. Post-intervention assessments will be conducted at the second and fourth week after the intervention using the same questionnaire used in the pre-intervention assessment.

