### The control groups

Participants in the non-specific acupoint group will follow the exact same procedure as the treatment group.

Participants in the blank control group will be instructed to maintain their regular daily routines, enabling the isolated effect of ARAT to be analyzed. If the results of the study are favorable, participants in the two control groups will be offered the opportunity to receive ARAT free of charge.

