### Safety assessment

Participants will be asked to report any AEs, which are defined as any undesirable experiences [36]. They will have access to the research team members at any time. The occurrence time, severity, management, and causality of AEs will be recorded on CRFs. All AEs will be followed up until resolved, and severe AEs will be reported to the Ethics Committee of SCCGZUCM within 24 hours. Monitoring AEs in this trial serves the purpose of ensuring participant safety and dealing with adverse events in a timely manner, in addition to being a secondary outcome measure.

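### Adverse events rest on self-report, but only the two acupressure arms have weekly live contact, so the adverse-event comparison with the blank arm is open to unequal ascertainment

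*Protocol article*

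**What the plan says.** **Contact in the acupressure arms.** The protocol article's section on the ARAT group provides for weekly live contact over the 4-week treatment period: "participants will undergo weekly video-call check-ins to monitor their acupressure technique". It adds an app contact around each of the 20 sessions: "Participants will be asked to check-in at the start and end of each session". The section on the control groups extends this to the second acupressure arm: "Participants in the non-specific acupoint group will follow the exact same procedure as the treatment group".

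**Contact in the blank arm.** The same section says "Participants in the blank control group will be instructed to maintain their regular daily routines" and describes no calls or check-ins. This arm does have the app, because the health education given to all three groups uses it: "The program will be delivered through a video that will be accessible to participants via an app for convenient review". It also shares the common TNSS and RQLQs assessments at the beginning, middle and end of treatment and at follow-up weeks 4, 8 and 12.

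**Adverse events.** Under Secondary outcome measures, "AEs will be monitored through self-reporting by the participants". Safety assessment repeats the method for participants generally: "Participants will be asked to report any AEs, which are defined as any undesirable experiences", and "They will have access to the research team members at any time". The Outcomes section says that outcomes will be compared between groups. Apart from TNSS and RQLQs, measures are assessed at the beginning and end of treatment.

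**Blinding.** The Blinding section states that neither investigators nor participants are blinded to the intervention.

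**Relief medication.** The Ethical approval section requires participants to keep a diary of its use, without distinguishing arms.

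**The concern.** How many self-reported events are recorded depends on how often, and how directly, a participant has occasion to mention one. Two arms have about four scheduled live conversations with staff during treatment that the third lacks. The definition of an adverse event is broad, so minor complaints count, and these are the events most likely to go unmentioned unless there is an occasion to raise them. The calls check technique, and the protocol describes correct technique partly by sensations that include slight soreness, so discomfort is a natural topic on them.

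All three arms receive the same nasal spray and may use the same antihistamine, so background events can occur in every arm. If they are recorded more completely in two arms, an excess over blank could be read as an effect of acupressure when it reflects the chance to report. No later analysis can recover events that were never recorded, so this has to be settled at data collection.

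**Working it through.** The plan has no figure of its own on this point to reproduce. The check has two parts: a comparison of the arms, and an illustration of size.

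**1. Reporting opportunity by arm, treatment period**

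| | ARAT | Non-specific | Blank |
|---|---|---|---|
| Asked to report events; team reachable at any time | yes | yes | yes |
| Common assessments (beginning, middle, end) | yes | yes | yes |
| Weekly video calls (about 4) | yes | yes | none described |
| App check-in at start and end of 20 sessions (2 × 20 = 40) | yes | yes | none described |
| Relief-medication diary | yes | yes | yes |

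The first two columns are identical, so ARAT versus non-specific acupoints is balanced. The asymmetry is confined to comparisons with blank. The diary row has no asymmetry.

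**2. Size under stated assumptions**

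From the protocol: 37 per arm (33/(1 − 0.10) = 36.7, rounded up; 3 × 37 = 111).

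Assumed, because the protocol gives neither: true risk *p*, equal in both arms; capture fraction *c1* = 0.80-0.90 with calls and *c0* = 0.50-0.70 without.

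- Expected recorded events per arm = 37 × *p* × *c*
- Apparent risk ratio = (*p* × *c1*)/(*p* × *c0*) = *c1*/*c0*, which does not depend on *p*

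Corners of the assumed range:

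- 0.80/0.70 = 1.14
- 0.90/0.70 = 1.29
- 0.80/0.50 = 1.60
- 0.90/0.50 = 1.80

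Expected counts at *p* = 10% (37 × 0.10 = 3.7 true events per arm):

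- with calls: 3.7 × 0.80 = 2.96 to 3.7 × 0.90 = 3.33
- without calls: 3.7 × 0.50 = 1.85 to 3.7 × 0.70 = 2.59
- gap: 2.96 − 2.59 = 0.37 to 3.33 − 1.85 = 1.48 events

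False-positive rate of an uncorrected two-sided chi-square test at 0.05, 37 per arm, by exact enumeration of the two binomial distributions:

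| True risk in both arms | 90% vs 90% captured | 90% vs 70% | 90% vs 50% |
|---|---|---|---|
| 10% | 5.8% | 6.8% | 10.6% |
| 20% | 5.1% | 7.7% | 17.3% |
| 30% | 5.0% | 9.1% | 24.2% |

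With equal capture the test stays near its nominal level. With unequal capture the error ranges from slight to substantial, depending on quantities that the protocol does not fix.

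**The case against.** **The calls are not an adverse-event instrument.** Their stated purpose is technique monitoring. Nothing says that events are asked about or recorded on them, and the same is true of the session check-ins. All participants are asked to report events and can reach the team at any time. This stands against any reading that the comparison *is* biased: the text shows an opening for bias, not its presence. It does not remove the opening, because open access depends on the participant's initiative whereas a weekly call is scheduled live contact.

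**The blank arm is not without contact.** It has the common mid-treatment and end-of-treatment assessments, and Table 1, whose content was not available for this check, may list a common adverse-event enquiry. This is fair. If such an enquiry exists, the point shrinks to basing the comparison on it. The text itself describes only self-report.

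**Relief medication.** A reader might infer that the relief-medication score is affected too. The documents do not support that: use is recorded in diaries with no difference by arm, and the calls are not described as a source of medication data. An indirect effect of calls on diary completion is conceivable but not in the text.

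**Direction and weight.** Over-recording under acupressure works against the intervention, so the likely error is not a falsely reassuring safety result. The outcome is secondary, the trial calls itself exploratory, and no passage says that the safety conclusion rests on the blank arm alone. All of this stands and limits the consequence. A spurious excess against blank would still be a wrong result.

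**Conclusion.** The point holds for adverse events and for the two comparisons with the blank arm. Self-report, an open-label design and weekly live contact in only two of three arms leave those comparisons open to differential ascertainment, probably towards more events recorded under acupressure. ARAT versus non-specific acupoints is not affected.

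The size cannot be determined from the protocol. Under the assumed capture of 80-90% with calls and 50-70% without, the apparent risk ratio is about 1.14 to 1.80 with no true difference. At the low end, with 10% true risk, that is less than half an event per arm. The calculation assumes that true risk is equal and that only capture differs.

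It would be tempting to conclude that the safety results are invalid or that the recorded excess is certain. The documents support neither.

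**What to change.** Add one short adverse-event question set, with identical wording and on the same days in all three arms, delivered through the app that every arm already uses or as a page in the existing diary. Weekly timing would match the calls. State in the outcome section that the between-arm adverse-event comparison uses only this common instrument, and that events surfacing only during technique calls are recorded and reported separately. The blank arm needs no calls. If Table 1 already schedules such an enquiry in all arms, a sentence tying the comparison to it is enough.

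The cost is one short form and one or two sentences of text. The small downsides are slightly more burden on participants and a little more contact for the blank arm.
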